## Abstract

**Introduction:**

A relevant subsample of patients with chronic low back pain (CLBP) have manifested augmented central pain processing, central sensitisation (CS). Patients with CLBP have limited functioning and participation. Theoretically, physical functioning in patients with CLBP can plausibly be linked to CS; however, evidence to explain such association is scarce. Moreover, there is no gold standard for CS diagnosis. The objectives of the study are: (1) to analyse the association between instruments assessing reference symptoms and signs attributed to CS; (2) to analyse whether reference symptoms and signs attributed to CS are associated with functioning measurement outcomes; and (3) to analyse whether changes (between baseline and discharge) in reference symptoms and signs attributed to CS are related to changes in each of the functioning measurement outcomes.

**Methods and analysis:**

A cross-sectional and longitudinal observational study is performed with measurements taken at baseline and discharge of an interdisciplinary rehabilitation programme. A sample size of 110 adult patients with CLBP has been calculated for the study. CS measurements are: Central Sensitisation Inventory, quantitative sensory testing and heart rate variability. Functioning measurements are: lifting capacity, maximal aerobic capacity, accelerometry and reported functioning. Statistical analyses to be performed are: (1) correlation between CS measurements, (2) multiple regression between functioning (dependent variable) and CS measurements (independent variable), and (3) multiple regression between changes in scores of functioning (dependent variable) and CS measurements (independent variable), and corrected for sex and age.

**Ethics and dissemination:**

The study obtained the clearance to its implementation from the Medical Research Ethics Committee of the University Medical Center Groningen in July 2017. The results will be disseminated through scientific publications in peer-reviewed journals, presentations at relevant conferences, and reports to stakeholders.

**Trial registration number:**

NTR7167/NL6980.

Strengths and limitations of this studyNovel and comprehensive approaches for the assessment of the presence of central sensitisation (CS).Extensive amount of measurements from multiple domains for the determination of functioning status.Longitudinal study with measurements at baseline and discharge of an interdisciplinary rehabilitation programme implemented as ‘Care As Usual’.Strategies allocated to promote participation and adherence, and to mitigate selection bias to the largest extent possible.Statistical analyses are performed with selections of CS and functioning measurements, and these selections may influence study results.

## Introduction

### Background

Twenty per cent of the general population experiences prolonged or recurrent pain for at least 3 months, such pain is then considered to be chronic.^1 2^ Low back pain is the principal cause of years lived with disability and workdays lost in Europe and worldwide,^3^ and its sequelae affect 9% of the global population.^4^ Moreover, although there are several treatment intervention strategies available for patients with chronic low back pain (CLBP), treatment effect sizes have only been moderate.^5^ Such evidence may explain why 40% of the patients are not satisfied with the treatment received.^2^ The economic consequences of chronic pain include direct costs of medical care and pain management treatments, as well as indirect costs of decreased work productivity and sick leave, and of disability and sickness retirement.^2 6^ The indirect costs determine 86%–88% of the total costs produced by patients with CLBP.^7 8^ In particular, in the Netherlands, the costs derived from back pain to Dutch society were 3.5 billion in 2007, corresponding to 0.6% of the gross national product.^8^

In the past decennia, a relevant subsample of patients with chronic pain, including individuals with CLBP, have shown an increased responsiveness to noxious and non-noxious stimuli, described as central sensitisation (CS).^9^ CS is a result of an imbalance in the nociceptive pathways (‘pain pathways’) and supraspinal structures due to an amplified facilitation and/or reduced inhibition.^10–12^ The phenomenon, CS, is manifested by an amplified pain perception regarding its intensity (hyperalgesia and allodynia), duration (aftersensations and temporal summation) and distribution (expansion of the receptive field), as well as a reduced conditioned pain modulation (CPM).^12^ There is currently no gold standard for CS diagnosis. Identifying reference clinical symptoms and signs, however, may indicate the presence of CS: disproportionate pain, diffuse distribution, allodynia and hyperalgesia, hypersensitivity unrelated to mechanical stimulus but rather to environmental sensations (light, temperature, noise or other stressors), maladaptive psychosocial factors and low vagal nerve activity.^13–16^

Chronic pain is a multifactorial condition which has an impact on physical or body structures and functions, on psychological processes and on daily activities and quality of life of individuals.^2 17 18^ Limited functioning or capacity to perform everyday tasks (essential for an independent living) affects individuals with chronic pain in their mobility and self-care, social relationships, work and leisure.^19^ Individuals’ functioning is composed of body functions (body level)—described by impairments they experience—and of activities and participation (personal and social levels, respectively)—described by capacity and performance tests.^18 20^ An extensive overview of the functioning status is best obtained when the assessment includes suitable and relevant measures from multiple domains of daily living. In particular, lifting capacity, physical activity (PA), aerobic capacity or daily activities participation are measures that account for the multiple operationalisations of functioning in the daily living.

Patients with CLBP are likely to be less physically active, and be more deconditioned and disabled.^3 21–23^ A subsample of patients with CLBP can manifest symptoms and signs of CS being present.^9^ Because patients with CS are more reactive to stimuli and their pain experience is enhanced, the presence of CS and/or higher levels of CS could plausibly be associated with lower physical functioning and participation in patients with CLBP, and vice versa. More severe symptomatology of CS, decreased parasympathetic/vagal activity or altered somatosensory responses have been associated with greater self-reported pain-related disability.^24–30^ However, the associations between altered somatosensory responses and self-reported disability were dependent on the site of testing, the stimuli and the type of tests performed. Also, CS has been assessed with different instruments that measure specific CS clinical symptoms,^12^ lacking a comprehensive assessment of CS in which various reference clinical symptoms are measured together. Moreover, functioning has most frequently been assessed with self-reported disability which is not exclusively representative of the functioning status of the patient.

The study described in this research protocol has been created to improve the assessment and management of pain and disability of centrally sensitised patients with CLBP and fill the existing gaps in knowledge. On the one hand, it intends to assist on the phenotyping of centrally sensitised patients with CLBP. To this purpose, an integrated assessment of CS combining the use of various instruments which measure different reference clinical symptoms of CS is aimed. Instruments like Central Sensitisation Inventory (CSI),^31^ quantitative sensory testing (QST)^32 33^ and heart rate variability (HRV)^34^ are non-invasive, feasible and assess different reference clinical symptoms and signs indicative of CS.^12^ In the absence of a gold standard, these instruments measure different reference indicators of CS and can also be complementary to describe CS. On the other hand, it intends to improve the understanding of CS phenomenon and its contribution to functioning status. Lifting capacity, PA levels and/or PA distribution or patterns, aerobic capacity and daily activities participation are representative of several tasks of the daily living usually limited in patients with CLBP. These capacity and performance tests and self-reported functioning measures can give an extensive overview of the functioning status.

### Objective(s)

The objectives of the studies covered by this research protocol are:

To analyse the association between three instruments assessing reference symptoms and signs attributed to CS in patients with CLBP: CSI, QST and HRV.To analyse whether reference symptoms and signs attributed to CS are associated with functioning measurement outcomes in patients with CLBP. Specifically, to analyse the association between the three instruments assessing CS (CSI, QST and HRV) and: lifting capacity, aerobic capacity, PA levels and/or PA distribution or patterns, and patient-reported measurements.To analyse whether changes (between baseline and discharge) in reference symptoms and signs attributed to CS are related to changes in each of the functioning measurement outcomes in patients with CLBP. Specifically, to analyse whether decreases in CS described as: a lower CSI score, an increase in the pain thresholds (QST) and an increase in parasympathetic/vagal tone (HRV) are related to a better functioning described as: an increase in lifting capacity, an increase in aerobic capacity, an increase in PA levels and/or a change in PA distribution or patterns, and better outcome scores in patient-reported measurements.

## Methods and analyses

### Study design

An observational study project with both cross-sectional and longitudinal designs is being conducted from September 2017 to September 2019 in the Center for Rehabilitation of the University Medical Center Groningen (CvR-UMCG) in the Netherlands.

### Patient and public involvement

The personnel of the CvR-UMCG collaborate in the study, in particular, the Pain Rehabilitation team during patient management and data collection process and the central exercise lab team on data collection process. The authors wish to express their gratitude to the collaborators and to the patients who participate.

### Participants

Consecutive patients between 18 and 65 years of age at the time of recruitment who are primarily referred to the outpatient Pain Rehabilitation Department of the CvR-UMCG due to a chronic primary low back pain and who are assessed for the interdisciplinary pain rehabilitation programme are eligible to participate in the study. Chronic primary low back pain is defined as a low back pain recurrent for more than 3 months, related to emotional distress and/or functional disability and whose pain is not a result of any other diagnosis^35^ even if patients may have undergone surgery in the past. Additionally, patients are invited to the study if they are mentally competent and can follow instructions. Furthermore, patients are excluded from the study if, based on their file, they: have a specific diagnosis that would better account for the symptoms (cancer, osteoporosis, rheumatological inflammatory diseases and/or spinal fractures), have neuralgia and/or radicular pain in the legs, have severe psychiatric disorders, show sensitivity alterations in measurement location(s), are pregnant (or planning to be), have any specific contraindication according to the standards of practice guidelines of the assessments that they are going to be subjected to,^36 37^ or take any medication that may interfere with the assessment outcomes such as calcium channel blockers on HRV. CS-related comorbidities (ie, fibromyalgia, osteoarthritis or chronic fatigue syndrome) are no reason for exclusion from the study. The use of opioid or pain-related medication is neither a criterion for exclusion and such information is recorded.

### Procedures

Measurements are performed as part of ‘Care As Usual’ (CAU) for outpatients following the pain rehabilitation guidelines of the CvR-UMCG. However, not all measurements of the research protocol belong to the battery of assessments of the CvR-UMCG, as pointed out in the legend of figure 1.

**Figure 1 F1:**
[figure not shown]
Flow chart of the project procedure. *Measurements obtained which do not belong to Care As Usual (CAU) of the Pain Rehabilitation Department of the Center for Rehabilitation of the University Medical Center Groningen (CvR–UMCG). CLBP, chronic low back pain; CSI, Central Sensitisation Inventory; HRV, heart rate variability; PDI, Pain Disability Index; QST, quantitative sensory testing; Rand36-PF, Rand36 Physical Functioning subscale; VAS, Visual Analogue Scale; WAS, Work Ability Score.

During the first appointment of the patients with the rehabilitation physician, patients are invited to participate in the studies if based on their file they are eligible according to the criteria defined for the studies. Eligible patients who are invited to participate and receive information about the study, but have not reacted, are contacted in a week’s time to remind them about the study participation. Those who sign the informed consent, fill in forms with their relevant personal information during the baseline assessment and are given vouchers for the travel expenses during the discharge assessment. Participating patients follow CAU trajectory with the Pain Rehabilitation team in terms of assessments, screening and implementation of the interdisciplinary rehabilitation programme. As part of the research protocol, the performance of additional assessments and filling up of questionnaires on CS and functioning are required. CSI, lifting capacity and HRV results are collected as CAU. Aerobic capacity, QST, objective PA monitoring, and pain intensity and functioning questionnaires’ results are collected as additional to CAU. All CS measurements, objective PA monitoring and capacity tests are measured at two time points, baseline and discharge. Pain intensity and functioning questionnaires, on the other hand, are measured at 13 time points, baseline and once a week during the 12-week rehabilitation programme. Pain Disability Index (PDI) is the only functioning questionnaire collected as CAU at baseline but as additional during the rehabilitation programme. A diagram of the project procedure is presented in figure 1.

### Measurements

#### CS measurements

In order to comprehensively assess the symptoms and signs attributed to CS, data are obtained from a questionnaire (CSI) and two physical assessments (QST and HRV).

##### Central Sensitisation Inventory

The inventory is a self-reported questionnaire with two sections to estimate the severity of CS-related symptoms. Section A is a 25-item questionnaire to assess the presence of the most common CS-related symptoms. Each of the questions is measured on a 5-point Likert scale from 0 (never) to 4 (always), and the total score ranges from 0 to 100, where higher scoring is associated with more severe symptomatology. Section B is a 10-item questionnaire to assess the previously diagnosed CS syndromes (CSS) and/or conditions related to CS. Higher amount of CSS is associated with higher chances of CS being present. This instrument has shown excellent test–retest reliability (intraclass correlation coefficient (ICC)=0.82–0.97) and internal consistency (Cronbach’s α=0.87–0.91) in the general population and in patients with chronic pain,^31 38–40^ as well as good concurrent validity (sensitivity=81%, specificity=75%) for CSS diagnosis within patients with chronic pain.^38^ For the purposes of the study the Dutch translation of the CSI is used,^41^ which has also shown excellent internal consistency (Cronbach’s α=0.91) and test–retest reliability (ICC=0.91 and 0.88) in controls and in patients with chronic musculoskeletal pain, respectively.^42^ The psychometric information of CSI in patients with CLBP is not known.

##### Quantitative sensory testing

A battery of standardised sensory tests quantifies the function of the somatosensory system. QST tests the characteristics of various sensation and nociceptive processes as representative of afferent nerve fibres and central pathways performance. The whole assessment lasts for 1 hour, and it consists of six sensory tests, which are measured in seven different predefined body locations: one training location to familiarise the patient with the tests, the most painful location (as pointed out by the patient), and five control locations. See online supplementary material 1 for full description of body locations. The standardised instructions of the sensory tests are read to the patient at each test performance. Of the tests, five consist of mechanical stimuli based on and performed following the QST examination of the German Research Network on Neuropathic Pain (DFNS) protocol,^32^ and one for CPM following the Nijmegen-Aalborg Screening QST protocol.^33 43^ Overall, the DFNS protocol has shown good test–retest (mean r=0.86) and interobserver reliability (mean r=0.83) in patients with affections in the somatosensory system either with or without pain.^44^ For the purpose of avoiding bias due to the order of the measurements and locations, a counterbalancing procedure is established, which accounts for the locations and the measurements to be made. This procedure provides three different assessment order groups, all of which begin with the measurements at the training location and end with the CPM test. An additional counterbalancing procedure has been made for allocating patients to these assessment order groups (either 1, 2, or 3). Every nine patients, a different allocation order is performed to ensure a similar amount of QST assessments per group. All assessors are trained in the QST protocol. The following sensory tests are performed:

10.1136/bmjopen-2019-031592.supp1Supplementary data

*Dynamic mechanical allodynia* (*DMA*)—to test the presence of abnormal stimuli-evoked pain—is assessed with a soft brush (SENSElab, Brush-05, Somedic, Hörby, Sweden) that is swiped 1–2 cm over the skin. This is performed on a single repetition and on a train of three repetitions (wind-up response). At each of the seven body locations (see online supplementary material 1) it is recorded whether the patients feel the sweeping and its pain intensity with a numeric rating scale (NRS) ranging from 0 (no pain) to 100 (most intense pain imaginable) for both the single swipe and the series.^45 46^ The DMA (ratio) is calculated as: DMA=(NRS-3/NRS-1). If NRS-1 is 0, the DMA for that location cannot be calculated and it will be registered as a missing value. The DMA test according to the DFNS protocol has shown to have good test–retest (r=0.87) and interobserver reliability (r=0.79).^44^

*Mechanical pain threshold* (*MPT*)—to test the ability to perceive sharp, pricking or stinging stimuli—is assessed with a set of standardised weighted pinprick stimulators with seven different intensities (the PinPrick Stimulator Set, MRC Systems, Germany) and with a modified method of limits. Starting at the lowest intensity (8 mN), it progressively increases until patients report the stimulus to change from touch to painful (sharp, pricking or stinging). The intensity of the pinprick that produces the first painful stimulus in millinewtons is recorded in each of the seven locations (see online supplementary material 1).^46–49^ The MPT test according to the DFNS protocol has shown to have good test–retest (r=0.80) and interobserver reliability (r=0.80).^44^

*Wind-up ratio* (*WUR*)—to test the nervous system’s painful stimuli temporal summation or responsiveness to repeated noxious stimuli. Such test is assessed with a suprathreshold pinprick stimulator of 256 mN (the PinPrick Stimulator Set, MRC Systems, Germany), which is applied on a single repetition and on a train of 10 repetitions in an area of 1 cm^2^ with intervals of 1 s (wind-up response). The pain intensity measured with an NRS ranging from 0 (no pain) to 100 (most intense pain imaginable) for both the single repetition and the series is recorded in each of the seven body locations (see online supplementary material 1).^50 51^ The WUR (ratio) is calculated as: WUR=(NRS-10/NRS-1). If NRS-1 is 0, the WUR for that location cannot be calculated and it will be registered as a missing value. The WUR test according to the DFNS protocol has shown to have poor test–retest (r=0.67) and interobserver reliability (r=0.56).^44^

*Mechanical detection threshold* (*MDT*)—to test the ability to detect light touch—is assessed with a standardised set of von Frey filaments (OptiHair2-Set, Marstock Nervtest, Germany) with a modified method of limits.^52 53^ Starting at the intensity of 16 mN, the stimulus application progressively decreases until patients do not report any sensation. The intensity of the filament that is not perceived in millinewtons is recorded in each of the seven body locations (see online supplementary material 1).^54^ The MDT test, according to the DFNS protocol, has shown to have good test–retest (r=0.90) and interobserver reliability (r=0.89).^44^

*Pressure pain threshold* (*PPT*)—to test the ability to perceive pressure pain stimuli on muscles—is assessed with an electronic pressure algometer (Force Ten FDX, Wagner Instruments, USA). With this tool, the pressure in the contact point (1 cm^2^ tip) is progressively but steadily increased until patients report to feel pressure change towards painful (burning, drilling or aching). The intensity in newtons when pressure becomes painful and its pain intensity with an NRS ranging from 0 (no pain) to 100 (most intense pain imaginable) scale is recorded in each of the seven body locations (see online supplementary material 1).^32^ The PPT test according to the DFNS protocol has shown to have good test–retest (r=0.88) and interobserver reliability (r=0.84).^44^

*CPM*—to test the nervous system’s descending pain processing. The CPM test methodology selected for this study follows the recommendations of the EFIC meeting (2013).^55^ The pain modulation is assessed by means of PPT tests (test stimuli) in a distant location from patients’ dominant hand (musculus deltoid and musculus quadriceps of the non-dominant side, see online supplementary material 1) before and after immersing the dominant hand in a bucket full with ice and cold water (cold conditioning stimuli). First, PPT measurements at distant locations are made; then, patients immerse the dominant hand in the bucket for as long as they possibly can with a maximal duration of 3 min; finally, PPT measurements are repeated. The PPT results, intensity in newtons and pain intensity with an NRS ranging from 0 (no pain) to 100 (most intense pain imaginable) scale, in both locations and the time the hand is immersed are recorded. The CPM (%) is calculated as: CPM=[(PPTpost–PPTpre)/PPTpre]∗100, where lower values indicate lower alteration on the nociceptive pathways.^33 43^ The CPM test, as the combination of the PPT handheld algometer and cold stimuli, has shown to be one of the most reliable methods with a modest test–retest reliability (ICC=0.49 and coefficient of variation=63.6%).^56^

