### Analyses

Data records from the different tests and questionnaires will be collected and merged into one database. The database management will be done by the project team and handled according to the internal regulations of the UMCG. The analyses of the study will be performed with SPSS software version 22.0 (IBM).

Before any analysis, data will be prepared:

Variables need to be calculated: body mass index; DMA, WUR and CPM tests (see the Methods and analyses section, Measurements: CS measurements); PDI, Rand36-PF, PCS, BSI and IEQ questionnaires.HRV: data will be preprocessed to correct for any artefacts that may be present at the beginning or at the end of the recording.QST: the overall value of each sensory test is the mean at the most painful location and the five control locations together, provided that at most two locations are missing.To perform the analyses to respond to objective 3, delta scores are computed (difference in scores between baseline and discharge) for CS, functioning and those confounder variables which are also measured at the same time points as the main measurements.

Proxies of the main measurements were selected to perform analyses. CS variables are: the sum score of CSI part A and the RMSSD for HRV. For QST, no variables are predefined, variables that correlate most strongly with each of the functioning measures will be selected. Functioning variables are: the maximal weight lifted for lifting capacity, the VO_2_max/kg for the maximal aerobic capacity, the daily vector magnitude (VM) counts for PA and the average score of Rand36-PF for reported physical functioning.

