Within the constraints of CAU and in the absence of a single gold standard instrument that can diagnose CS, in this research protocol multiple instruments have been selected to examine reference symptoms and signs attributed to CS. (1) The hypersensitivity unrelated to mechanical stimulus is assessed with CSI. A questionnaire designed to measure CS, as it has been shown to be associated to factors known to contribute to CS and is able to identify somatic and emotional symptoms related to CSS.^24 38 92^ (2) The disproportionate pain, diffuse distribution, and allodynia and hyperalgesia are measured with QST. The QST is a battery of non-invasive standardised tests that assists in the identification of sensory and pain thresholds, the determination of pain intensity perception and the assessment of the CPM. Its results can allow pain characterisation (phenotyping) and processing, and monitoring its progression.^93–97^ (3) The low vagal nerve activity is examined with HRV. A non-invasive standardised measure that characterises the function of the ANS.^34^ The somatic and emotional symptoms related to CSS may generate an imbalance between a hyperactivation of the sympathetic tone and a reduction of the parasympathetic/vagal tone.^34 98 99^ (4) Psychosocial factors are measured with psychological screening questionnaires for perceived injustice (IEQ), catastrophising (PCS) and psychological distress (BSI). These psychosocial factors have shown a consistent effect on functioning and on symptom beliefs and pain behaviours, which are common in patients with chronic pain, including CSS. Therefore, although not necessary for the clinical classification of CS, these factors are included in the study and potentially in the analyses. Some of the CS assessment instruments used in this study are more acknowledged than others in CS literature. CSI is widely used to measure CS since it was designed as a proxy for it; however, its internal consistency and reliability in patients with CLBP has not yet been made available. Also, evidence is currently piling up on the necessity of routinely implementing the elements of QST relevant to patients’ conditions in clinical practice, given its ability to assess the somatosensory function,^97 100^ even though evidence in patients with CLBP is limited. Finally, literature on HRV as an instrument that may reflect an imbalance of ANS in patients with chronic pain conditions (specifically in those patients who have shown an overlap in the CS symptoms) is scarce.^101^ We are confident that the selected CS assessment instruments are considered the best available and combined will be able to comprehensively measure from the different reference clinical symptoms and signs indicative of CS being present. This will provide further insights on the mechanisms of CS and assist on the phenotyping of centrally sensitised patients with CLBP.

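### DMA is scored as a brush wind-up ratio, NRS-3/NRS-1, which cancels the level of brush-evoked pain that the test is said to detect

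*Protocol article*

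**What the plan says.** Under Quantitative sensory testing, the article gives the purpose of DMA as "to test the presence of abnormal stimuli-evoked pain". The stimulus is a soft brush: "This is performed on a single repetition and on a train of three repetitions (wind-up response". Pain is rated on a numeric scale "ranging from 0 (no pain) to 100 (most intense pain imaginable) for both the single swipe and the series". The score is then fixed: "The DMA (ratio) is calculated as: DMA=(NRS-3/NRS-1". When the single-swipe rating is zero, "If NRS-1 is 0, the DMA for that location cannot be calculated and it will be registered as a missing value".

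Pinprick temporal summation has its own test, with a score of the same form: "The WUR (ratio) is calculated as: WUR=(NRS-10/NRS-1".

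The Analyses section lists the derived variables ("Variables need to be calculated: body mass index; DMA, WUR and CPM tests") and refers back to these formulas. Each sensory test is summarised as the mean over the most painful location and five control locations, with at most two missing. Objective 3 uses differences between baseline and discharge. No QST variable is fixed in advance; those correlating most strongly with each functioning measure are chosen. The Discussion states what the battery stands for: "The disproportionate pain, diffuse distribution, and allodynia and hyperalgesia are measured with QST".

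**The concern.** Whether brush pain is present, and how much there is, is contained in the two ratings themselves. Their quotient contains something else: how much the pain grew, in relative terms, from one swipe to three. That is a summation measure. The purpose sentence names one construct and the formula delivers another.

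This is separate from the rule for a zero denominator. That rule decides who has no score; the problem here concerns patients who do have one. Among them, the score need not rise with the amount of brush pain. If DMA is reported as the allodynia variable, a null or inverse association could be read as a finding about allodynia when it comes from the scoring. The selection step adds to this. DMA could be dropped because its score says little about brush pain, or kept with a coefficient that a reader would misinterpret.

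**Working it through.** The article states no numerical DMA result, so there is no figure to reproduce. The check applies the stated formula directly.

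**Inputs from the Quantitative sensory testing section:** score = NRS-3/NRS-1; both ratings run from 0 to 100; the score is missing if NRS-1 = 0. For contrast, a level score is shown: (NRS-1 + NRS-3)/2.

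| NRS-1 | NRS-3 | Ratio | Level score |
|---|---|---|---|
| 1 | 2 | 2.0 | 1.5 |
| 5 | 10 | 2.0 | 7.5 |
| 40 | 80 | 2.0 | 60 |
| 1 | 1 | 1.0 | 1 |
| 100 | 100 | 1.0 | 100 |
| 2 | 6 | 3.0 | 4 |
| 60 | 60 | 1.0 | 60 |
| 90 | 100 | 1.11 | 95 |
| 5 | 6 | 1.2 | 5.5 |

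**Step 1, cancellation.** If both ratings are multiplied by the same factor k, the ratio is k·NRS-3/(k·NRS-1) = NRS-3/NRS-1. The first three rows share a score of 2.0 although brush pain differs up to 40-fold.

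**Step 2, ceiling.** NRS-3 cannot exceed 100, so the ratio cannot exceed 100/NRS-1. This is 100 at NRS-1 = 1, 10 at 10, 2.0 at 50, 1.25 at 80 and 1.0 at 100. The highest attainable score falls as single-swipe pain rises.

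**Step 3, change scores.** From 60/60 to 10/10 the ratio goes from 1.0 to 1.0, a change of zero, while the level score falls by 60 − 10 = 50 points. Zero change requires both ratings to fall by the same proportion. From 60/60 to 10/20 the ratio rises from 1.0 to 2.0 although pain fell. From 40/80 to 10/10 it falls from 2.0 to 1.0, in the same direction as the pain.

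**Step 4, how often the order reverses.** Take trivial as NRS-1 from 1 to 10 and severe as NRS-1 from 50 to 100 (assumed cut-offs, whole-number ratings).
- With equal absolute increments of 0 to 20 points, the severe patient scores the same or lower in 8,610 of 8,610 pairs.
- With free increments (trivial NRS-3 up to 20, severe up to 100), this happens in 178,509 of 205,530 pairs, or 87%.
- Counter-example: 40/80 gives 2.0, above 5/6 at 1.2.

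These are counts over a grid, not predicted frequencies in patients.

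**Step 5, correlation with brush pain.** The article gives no distribution of brush ratings, so every model here is an assumption (200,000 simulated patients in the first two sets).
- NRS-1 lognormal, median 10, log-SD 0.9. Spearman correlation of the ratio with mean brush pain is −0.67 if the train adds an increment (median 5, log-SD 0.6) and 0.16 if it multiplies pain (log-mean 0.3, log-SD 0.3).
- Pain level lognormal, median 15, log-SD 0.9. Correlation of the ratio with that level is −0.72 if the train adds (mean 5, SD 3) and −0.07 if it multiplies (median factor 1.3, log-SD 0.25).
- Proportional wind-up itself correlated with pain level at 0.2, 0.4 or 0.6: the correlation with mean brush pain becomes about 0.32, 0.48 or 0.63.

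The range is roughly −0.7 to +0.6. Steps 1 and 2 depend on none of these assumptions.

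**The case against.** **The ratio may be deliberate.** The article labels the three-swipe train a wind-up response and calls the variable a ratio. The Background lists temporal summation beside allodynia as a manifestation of central sensitisation, and WUR covers pinprick rather than brush summation, so a brush ratio is not redundant. This stands as an explanation of the formula. It does not reconcile the formula with the stated purpose. The Discussion credits allodynia to the battery as a whole, but DMA is its only brush test.

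**The published protocol is followed.** The article cites that protocol for the examination procedure and for reliability. Reliability shows that a result is repeatable, not that the ratio measures the presence or level of allodynia.

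**The reach is limited.** DMA is one of six candidates and may enter no regression. A patient needs a value at four or more of the six sites, hence single-swipe brush pain at three or more control sites. The Participants section excludes neuralgia, radicular leg pain and sensitivity alterations at measurement locations. The scored group may therefore be small, and missing values may be the larger difficulty with DMA. All of this stands and limits the weight of the point. The raw ratings are also recorded, so nothing is lost irretrievably.

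**Stronger readings go too far.** A reader might infer that severe allodynia always scores no higher than trivial allodynia, that any improvement in brush pain yields a zero change, or that an association would take the wrong sign. The formula supports none of these as a general statement. The pair 40/80 outscores 5/6, a zero change needs proportional falls, and the sign varies with distributions that the article does not report.

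**Conclusion.** The mismatch is real and rests on the article's own text. The stated construct is brush-evoked pain, the derived variable is relative brush wind-up, and the article defines no score for the presence or level of brush pain. The cancellation and the ceiling of 100/NRS-1 are exact. Patients with severe allodynia can score the same as or lower than patients with trivial allodynia, and a proportional improvement is invisible in the change score.

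The effect on the study's associations cannot be sized from the article. Under the assumed models, the ratio's correlation with brush pain runs from about −0.7 to about +0.6, so an association with allodynia could be missed or distorted, without a predictable direction. DMA's role as one unselected candidate among six keeps this a derivation rule that should be corrected, not a threat to the study as a whole.

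**What to change.** Derive the allodynia variable from the ratings already taken: at each site the mean of NRS-1 and NRS-3, then the average over the six analysed sites. This score is also defined when NRS-1 is 0. Analyse it by ranks, or as present/absent if most values are zero; the binary form is closest to the stated purpose. Other level scores, such as either rating alone or the larger of the two, would also serve, provided one is named before the data are examined. If the ratio is kept, label it brush wind-up and do not use or report it as the allodynia measure.

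The cost is one line in the derivation rules and no new measurement. The downside is that the level score will be skewed and probably zero-inflated. A log(x+1) transformation would not cure a large share of zeros, which is why ranks or the binary form are suggested.
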